### 2.7. Sample Size and Data Analysis

The sample is calculated with the sample size calculation of Willan [40]. Like many of the parameters that were used, these were unknown, and assumptions were made about health parameters as the difference between the average cost of both treatments was assumed in monetary terms from EUR 300, and the standard deviation of the monetary costs was EUR 600. In addition, the effect of the intervention and the difference between means, to be detected in NDI, is 7 units, having a common variance in NDI in patients with neck pain of 10, which is a clear overestimation of the standard deviation. The correlation coefficient between effectiveness and cost is 0.1, clearly underestimated so that the sample size is increased, with an alpha error of 0.05 and a power of 80%. With these conditions, the sample size was 105 patients with neck pain per group (telerehabilitation programme group and face-to-face programme group). In each group, these patients will be divided into three subgroups (postural, dysfunction, and derangements syndromes).

We will register the number of days that patients are on sick leave due to neck pain, family cost, primary and secondary healthcare consultations (Andalusian Health Service provider), diagnostic test (Andalusian Health Service provider), additional medical services (Andalusian Health Service provider), material provided in intervention (production cost), and direct non-healthcare cost (aid to patients who face disabilities), and work absenteeism cost will be measured using days of work sick leave by salary.

### 2.8. Economic Evaluation

An economic analysis will be performed in STATA 19, including a CEA and a CUA, with the aim of estimating and comparing the incremental costs and benefits of the telerehabilitation and face-to-face care programmes. A six-month time horizon was chosen to capture not only the immediate effects of the interventions but also the costs and outcomes that arise during the months following their implementation. This duration allows a more comprehensive assessment of the interventions’ impact from a societal perspective. Missing cost data will be handled using appropriate techniques, such as multiple imputation, according to the type and magnitude of the missing data. We will use multiple imputation by chained equations. The imputation model will include all variables used in the CEA and CUA, assuming that data are missing at random. We will generate 20 imputed datasets, each analysed separately using the same statistical procedures. The results will then be pooled according to Rubin’s rules, providing unbiased estimates of variances that account for the uncertainty associated with imputed values. Given that the cost distribution is usually skewed due to the presence of patients with very high costs, the mean cost per patient will be presented together with confidence intervals obtained using non-parametric bootstrap methods [41]. QALYs will be calculated as the area under the curve connecting the utility scores recorded at baseline and at subsequent follow-up points. The results will be expressed as incremental cost-effectiveness ratios (ICERs), which reflect the additional cost per each additional unit of outcome achieved. An incremental analysis will be performed to calculate the difference in costs and the difference in outcomes (improvements in effectiveness measured in QALYs) associated with the telerehabilitation and face-to-face programmes. In order to address the uncertainty associated with sample variability, the joint distribution of the differences in costs and effects will be estimated through multiple simulations using non-parametric bootstrap methods. The simulated cost-effectiveness pairs will be graphically represented on a cost-effectiveness plane, and acceptability curves will be generated to reflect the probability that each alternative is cost-effective according to different willingness-to-pay thresholds per QALY [42]. In Spain, the value of a QALY is estimated to be between EUR 22,000 and EUR 25,000 [43]. A sensitivity analysis will be carried out to assess the robustness of the results against different values, assumptions, and methodological approaches [44]. As the time frame of this study is limited, it will not be necessary to apply discounting to costs or benefits. The economic analysis will be reported in accordance with the guidelines of the Consolidated Health Economic Evaluation Reporting Standards (CHEERS) [45].

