The telerehabilitation programme will use a support system for the treatment of cervical pain based on web technologies, accredited as a healthcare website. This system has a structure based on four sections: database management, database user profiles, recommendations, and feedback/biofeedback procedures. This system allows for registering and entering a subject and modifying a treatment with electroanalgesia and exercises, according to the symptomatic evolution of the pain. It is based on an initial patient assessment system. Once the initial diagnosis of the patient is made according to the McKenzie clinical subtypes of NP, a multimedia database will be developed with examples of specific treatments (according to symptom evolution) for postural syndrome, dysfunction syndrome, and derangement syndrome. Patients will use their computer or mobile device connected to the internet to access the platform, where they will find the videos of the combined application of electroanalgesia and exercises. The treatments will be provided by the system. The database is configured to accommodate the application of electroanalgesia and exercises based on the diagnosis according to the McKenzie method. Each subgroup corresponds to a programme and a set of previously defined exercises with electroanalgesia as well as recommendations for daily activities, such as manual activity, sitting, standing, or ergonomic postures for daily activities. Therefore, each treatment will use a feature vector VT with 3 characteristics (one for each subgroup), where each position will contain a value indicating the degree of difficulty for each treatment subgroup. The system calculates and recalculates recommendations and updates the values of the relevance estimates for the recommended treatments. The system will recommend treatment Y for subject X, and depending on the modification or remission of the pain, at the start of each session, it will continue with the same plan or will be adjusted following the therapeutic algorithm of the McKenzie method. Once the treatment is completed, the outcome measures will be evaluated. This evaluation will be recorded in the system to be subsequently available in the recommendation processes. Furthermore, the system recalculates the evaluations provided by the patients. To facilitate the correct execution of the treatment, each element on the website is arranged in the order in which it should be performed and represented by icons that are easily associated with each step. This ensures that patients are guided intuitively as they scroll through the website. To verify attendance and ensure that patients complete all sessions properly, patients must enter their ID in the field provided on the website at the end of each session. This confirmation will be emailed automatically to the responsible clinician.

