## Figures and Tables

**Table 1 healthcare-13-03076-t001:** Cost measures.

Costs	Breakdown	Source of Cost/Unit	Cost Calculation
Direct Medical Costs			
Primary care	General medicine	Andalusian Health Service	No. of visits × rate per visit
	Nursing		
	Physiotherapy		
Emergency hospital visits	General medicine	Andalusian Health Service	No. of visits × value per visit
	Nursing		
Referrals to services	Traumatology, Rehabilitation, etc.	Andalusian Health Service	Specialty × fee per visit
Home assistance	Ambulance	Andalusian Health Service	Service × fee-for-service
	General medicine		
	Nursing		
Diagnostic tests	X-rays, MRI, CAT Scans, etc.	Andalusian Health Service	Test × test price
Medicines	Muscle relaxants, analgesics, NSAIDs, etc.	Standard drug prices according to the Official General Council of Pharmacists	Medicine × price of the medicine
Non-medical direct costs			
Patient’s transport expenses	Bus	Patient	Number of times × price each time
	Taxi		
	Own transport (petrol)		
Indirect costs			
Absenteeism	Sick leave days	Patient and according to the assigned professional classification (National Statistics Institute of Spain)	Days of sick leave × daily wage

Magnetic resonance imaging (MRI), computed axial tomography (CAT), non-steroidal anti-inflammatory drugs (NSAIDs).

**Table 2 healthcare-13-03076-t002:** Timepoints of assessments.

Timepoint	Study Moment										
	Enrolment	Treatment								Follow-up	
	0W	1W	2W	3W	4W	5W	6W	7W	8W	2M	6M
	July 2025	July–September 2025								September 2025	January 2026
Screening and enrolment											
Eligibility screening	X										
Informed consent	X										
Allocation	X										
McKenzie classification	X										
Interventions											
Telerehabilitation programme (experimental)		3 Times per week									
Face-to-face programme (control)		3 Times per week									
Assessments											
Demographic variables		X									
Economic evaluation		X								X	X

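### Section 2.8 rests missing at random on the CEA and CUA variables and commits to no auxiliary predictor of drop-out

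*Protocol article*

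**What the plan says.** Section 2.8 opens with some latitude: "Missing cost data will be handled using appropriate techniques, such as multiple imputation, according to the type and magnitude of the missing data". It then commits: "We will use multiple imputation by chained equations". The content of the model and the assumption behind it come in one sentence: "The imputation model will include all variables used in the CEA and CUA, assuming that data are missing at random". The remaining settings follow: "We will generate 20 imputed datasets, each analysed separately using the same statistical procedures", with pooling by Rubin's rules. Later in the section there is a general promise: "A sensitivity analysis will be carried out to assess the robustness of the results against different values, assumptions, and methodological approaches". It names no departure from missing at random and no alternative imputation model.

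Other sections describe variables that could predict who is missing. In section 2.4, website users in the telerehabilitation arm confirm each session by typing in an identifier; the stated purpose is: "To verify attendance and ensure that patients complete all sessions properly". Table 2 lists "McKenzie classification" at enrolment. Section 2.2 names three recruiting sites. Section 2.9 has adverse effects recorded and takes a participant with a severe one out of the study. Section 2.5 requires both arms to come in person for every assessment.

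**The concern.** Missing at random is an assumption conditional on what the imputation model contains. The model here is described by what the economic analysis needs, and nothing is named because it predicts missingness. A patient lost before week 8 may leave little beyond baseline values and the arm to impute from.

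The design gives reasons to think that drop-out could depend on more than that. One arm is self-administered at home and the other is delivered by therapists in clinics, yet both must travel to the assessments. Withdrawal after a severe adverse effect is an explicit route to missing data, although the protocol calls that risk very low. If such a route also relates to cost or utility and works differently by arm, the imputed values are wrong by different amounts in the two arms. The error then enters incremental cost, incremental QALYs and the acceptability curve.

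**Working it through.** **1. Candidate predictors against the stated model**

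| Variable | Where it appears | Held for a patient who does not return? |
|---|---|---|
| Centre | Section 2.2 | Yes |
| McKenzie subtype | Section 2.3, Table 2 (enrolment) | Yes |
| Adverse effect, withdrawal | Section 2.9 | Yes, if recorded as planned |
| Sessions, telerehabilitation | Section 2.4, website confirmation | Yes |
| Sessions, face-to-face | No log described; visit and trip counts in Table 1 | Not from participant questionnaires (section 2.6); clinic records would be needed |

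The article does not list the CEA and CUA covariates. Centre or subtype might therefore already be among them; this cannot be settled from the text.

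**2. Bias in the cost difference**

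The plan gives no drop-out rate and no predictor of drop-out, so it has no figure to reproduce. From section 2.7: cost difference EUR 300, SD EUR 600, 105 per arm. Everything else here is assumed.

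Let *a* be standardised attendance, unrelated to baseline cost, with cost falling as attendance rises (correlation of size ρ). An imputation model without *a* leaves each arm mean off by −600·ρ·E[*a* | observed], so

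bias in difference = −600·ρ·(E[*a* | observed, tele] − E[*a* | observed, face-to-face]).

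Drop-out is logistic in *a* with slope −1.5 per SD and intercept 1.25 × the logit of the nominal rate. Integrating over a standard normal *a* gives E[*a* | observed] = 0.139, 0.250 and 0.347 at nominal drop-out of 10%, 20% and 30% (realised 12%, 22%, 32%). Where attendance does not drive drop-out, the term is 0. Example: 600 × 0.3 × 0.347 ≈ 62.

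Size of bias in EUR from the formula. In brackets, a simulation with 105 per arm, 20 imputations and 400 repetitions:

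| Drop-out tele / face-to-face | ρ = 0.1 | ρ = 0.3 | ρ = 0.5 |
|---|---|---|---|
| Tele arm only driven by attendance, 20 / 10 | 15 (18) | 45 (41) | 75 (76) |
| Tele arm only, 20 / 20 | 15 (13) | 45 (48) | 75 (77) |
| Tele arm only, 30 / 10 | 21 (21) | 62 (64) | 104 (102) |
| Same slope in both arms, 20 / 10 | 7 (14) | 20 (16) | 33 (32) |
| Same slope in both arms, 30 / 10 | 12 (16) | 37 (36) | 62 (57) |
| Same slope and rate, 20 / 20 | 0 (4) | 0 (2) | 0 (4) |

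Simulation error is about 83/√400 ≈ EUR 4 per cell, before the loss of data to drop-out. With attendance in the imputation model, the simulated bias was about EUR 10 or less in every case. In all rows except the last, the bias makes telerehabilitation look cheaper, but only because attendance was assumed to lower cost. Reversing that sign reverses the bias.

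**3. Net benefit**

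A separate large-sample simulation (400,000 per arm) valued QALYs at EUR 25,000. It assumed attendance 0.4–0.6 SD lower in telerehabilitation and final-visit missingness of 27–33% against 21%. The bias in net benefit was EUR 17.8–62.5 without attendance in the model and EUR 0.4–5.8 with it. With no arm difference in attendance it was −1.1 and −1.4, which is simulation noise.

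**4. Yardstick**

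Standard error of the cost difference with complete data: 600 × √(2/105) = EUR 82.8. A bias of EUR 13–21 is 0.16–0.25 of that, and EUR 41–64 is 0.50–0.77. The net-benefit figures are a different quantity and should not be divided by the EUR 300 cost difference.

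**The case against.** The strongest reply is that a model said to include all analysis variables is not limited to them. The same section lets the technique follow the missing data and plans sensitivity analyses, and a list of auxiliaries is detail that an article may leave to a full protocol or SAP. That stands against any claim of an error. It does not remove the point, because the article goes beyond silence: it states the model and the assumption that rests on it. Section 3 also says that analyses will not be modified after the first registration, apart from changes that are notified.

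Three stronger readings are tempting, and the documents support none of them.

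- A reader might infer that auxiliaries are ruled out. No such word appears.
- A reader might infer that missing at random fails. No drop-out rate, predictor of drop-out or attendance gap is given, and the Discussion cites comparable adherence for telemedicine programmes. That is background rather than trial data, but it points away from a gap.
- A reader might infer that the bias favours telerehabilitation. If programme sessions are costed, attending a clinic session adds physiotherapy and transport cost (Table 1), so the relation of attendance to cost may have the opposite sign in that arm.

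It can also be said that face-to-face attendance already enters through the visit and trip counts. This may be so, but section 2.6 collects those counts by participant questionnaire, so they may be missing for the same patients. The objection that session logging is described for one arm only stands in full and limits the fix.

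**Conclusion.** The point holds as a low-priority, low-cost improvement to a stated method, not as an error in the plan. Section 2.8 rests missing at random on a variable list that names no predictor of missingness, while the design records several. The assumption is less well supported than it could be; it has not been shown to fail.

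The possible bias in the cost difference runs from about zero (same mechanism and rate in both arms) to tens of euros under moderate assumed correlations. It reaches about EUR 100 only at a correlation of 0.5 with 30% drop-out driven by attendance in one arm alone. Except in that last case it is below one standard error. All of this rests on assumed drop-out rates, slopes and correlations, and the documents do not fix the direction.

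**What to change.** In section 2.8, after the words that tie the imputation model to the CEA and CUA, insert: *and, as auxiliary variables, centre, McKenzie subtype, early stopping or adverse effect, and number of sessions completed where recorded comparably in both arms; imputation will be run separately by arm*. Keep the missing-at-random statement, and name the model without auxiliaries as one of the sensitivity analyses. If auxiliaries were always intended, the edit only clarifies.

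Costs and limits:

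- The list must stay short. Centre (three sites) and subtype (three classes) take two terms each, stopping or adverse effect one and sessions one, six in all. At 30% drop-out, an arm of 105 leaves about 105 × 0.7 ≈ 74 observed patients to fit them.
- Home sessions are self-confirmed, so they predict imperfectly.
- Face-to-face sessions must come from clinic visit records, since no log is described for that arm. Without comparable records, leave sessions out and keep the other auxiliaries.
- Imputing by arm needs only coded groups, so the statistician can stay blinded.
- If the first participant is already registered, section 3 requires the change to be notified. It should be made before outcomes are seen by arm.

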### 2.6. Outcomes

The main outcome measure will be the healthcare resources used during the study, and their costs will be collected through questionnaires completed by the participants at baseline, post-treatment, and follow-up (6 months). Table 1 provides a detailed list of the relevant resource categories, the sources from which usage data are obtained, and the associated unit costs, Table 2 shows timepoints of assessments. The cost analysis will include resources and expenses related to primary and hospital care, diagnostic testing, and other direct out-of-pocket expenses incurred by the participants (e.g., transportation costs). In addition, the social costs associated with absenteeism and loss of productivity will be included as secondary outcomes. For each participant, information on their resource utilisation will be tracked by means of a receipt log. At each assessment, patients will be asked to recall and detail their use of the described resources during the preceding months. These data will then be converted into costs based on updated unit prices from official sources.

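### The trial is sized jointly on cost and NDI, but section 2.8 defines the incremental effect as QALYs only, so the cost-effectiveness analysis has no effect measure of its own and the 80% power was not derived for the QALY result

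*Protocol article*

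**What the plan says.** **Sizing (2.7).** A published cost-effectiveness sample-size method is cited. On cost, "the difference between the average cost of both treatments was assumed in monetary terms from EUR 300"; the assumed SD is EUR 600. On effect, "the effect of the intervention and the difference between means, to be detected in NDI, is 7 units". The NDI spread is 10, called both a variance and a standard deviation. The cost-effect correlation is 0.1, alpha 0.05 and power 80%, and the result is 105 per group.

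**Outcomes (2.6).** "The main outcome measure will be the healthcare resources used during the study", together with its costs. Absenteeism and lost productivity are secondary. Neither NDI nor a utility instrument is named.

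**Analysis (2.8).** Both a CEA and a CUA are announced. "The results will be expressed as incremental cost-effectiveness ratios (ICERs"), per additional unit of outcome, with no unit given. The incremental analysis then sets the cost difference against "the difference in outcomes (improvements in effectiveness measured in QALYs"). The acceptability curves run over willingness to pay per QALY, and the only threshold is EUR 22,000 to 25,000 per QALY.

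**Schedule (2.5 and Table 2).** Section 2.5 lists demographic and clinical data, resource use, costs and sick leave at three visits. Table 2 has rows for demographic variables and economic evaluation, and none for NDI.

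**The concern.** The Introduction separates the two analyses: cost-effectiveness weighs cost against how effective the treatment is, and cost-utility also brings in quality of life. That separation needs two effect measures. Section 2.7 supplies a clinical one, NDI, but 2.8 states the effect as QALYs and does not mention NDI.

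This is more than a detail left to a fuller document. Both sections fix the effect measure, and they fix it differently. A later analysis plan that used NDI for the CEA would depart from 2.8. One that followed 2.8 would leave the effect used for sizing unanalysed.

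Two things are at stake. The CEA and the CUA would share one denominator and so be one analysis under two names. And a reader would take the 80% to cover the cost-per-QALY result, although no QALY quantity entered the calculation.

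**Working it through.** **1. The effect measure, place by place.**
- 2.7: NDI, 7 units.
- 2.8, ICER sentence: generic unit of outcome.
- 2.8, incremental analysis, acceptability curves and threshold: QALY.
- 2.5, 2.6 and Table 2: NDI not named.
- Abbreviations: NDI listed.

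**2. Can 105 per group be reproduced?** Inputs from 2.7: cost difference 300, cost SD 600, NDI difference 7, NDI spread 10 (taken as an SD), correlation 0.1, power 80%. I assume a two-sided alpha of 0.05, so (1.96 + 0.8416)² = 7.849.
- Cost alone: n = 2 × 7.849 × (600/300)² = 62.8, so 63.
- NDI alone: n = 2 × 7.849 × (10/7)² = 32.04, so 33.
- Joint, assuming a net-benefit form with L = willingness to pay per NDI unit: n = 2 × 7.849 × [L²·10² + 600² − 2·L·0.1·10·600] / (7L − ΔC)².

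If the arm with the better NDI costs EUR 300 more (ΔC = 300):
- L = 10 gives 15.698 × 358,000/52,900 = 106.2.
- L = 100 gives 15.698 × 1,240,000/160,000 = 121.7.
- n = 105 is met at L of about EUR 9.8 or EUR 108 per NDI unit. If 10 is a variance (SD 3.16), the values are about 9.8 and 77.

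If that arm costs EUR 300 less (ΔC = −300), n is never above 63 for L from 0 to 22,000. Using the QALY threshold of 22,000 as if it were L per NDI unit gives about 32. So 105 depends on a willingness to pay per NDI unit and a direction of the cost difference, neither of which is stated. No variant uses a QALY input.

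**3. What 105 per group gives for the stated inputs taken singly.** √(2/105) = 0.1380.
- Cost: SE = 600 × 0.1380 = 82.8; 300/82.8 = 3.62; power = Φ(3.62 − 1.96) = 95%.
- NDI (SD 10): SE = 1.38; 7/1.38 = 5.07; power = Φ(5.07 − 1.96) = 99.9%.

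**4. Power for the QALY result.** The documents give no QALY difference (ΔQ) or QALY SD (s), so these are assumed ranges. With L = 22,000 per QALY, cost SD 600 and correlation 0.1, SE of net benefit = 0.1380 × √[(L·s)² + 600² − 2·0.1·L·s·600].
- s = 0.05: SE = 165.5.
- s = 0.10: SE = 306.6.
- s = 0.15: SE = 454.7.

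Power to show positive net benefit is Φ[(L·ΔQ − ΔC)/SE − 1.96], where ΔC is the extra cost of telerehabilitation.
- ΔQ = 0.03, equal costs: net benefit 660; 98%, 58% and 31% for s = 0.05, 0.10 and 0.15.
- s = 0.10, equal costs: 11%, 30%, 58% and 95% for ΔQ = 0.01, 0.02, 0.03 and 0.05.
- s = 0.10, ΔQ = 0.03: 22% if telerehabilitation costs EUR 300 more, 88% if it costs EUR 300 less.

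At EUR 25,000, the case s = 0.10, ΔQ = 0.03 and equal costs again gives 58%.

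**The case against.** **The sizing is joint.** Cost is an input, the declared main outcome is resource use and its cost, and mean costs with bootstrap intervals are planned. At 105 per group the EUR 300 difference alone has 95% power. This stands: a reader might infer that the power statement relates to nothing in the plan, and that is wrong. Only the effect part fails to carry over to QALYs.

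**NDI may well be collected.** Section 2.5 mentions clinical data, 2.4 says outcome measures will be evaluated, and section 3 says questionnaires will be scored. The article does not name its utility instrument either, so silence about an instrument proves little. This also stands: the documents do not support saying that NDI is not measured or that the CEA cannot be delivered. It does not remove the conflict, because 2.8 names the effect and names a different one from 2.7. The generic ICER sentence does not rescue it, since the sentence after it defines the outcome difference in QALYs.

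**The power figures are assumptions.** A reader might infer that the trial is underpowered for QALYs. The ranges above do not show that; they lie on both sides of 80%.

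**The ICER.** Both arms receive the same programme, so the effect difference may be near zero and the ratio unstable. It is tempting to call the ICER the wrong result. But 2.8 already plans a bootstrap of the joint distribution, the cost-effectiveness plane and acceptability curves, which largely deal with this. Making net benefit the primary result would be a preference, not a correction.

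**Conclusion.** The concern holds in a limited form. Sections 2.7 and 2.8 fix different effect measures. Followed as written, the CEA has no effect distinct from the CUA, and the NDI difference used for sizing has no analysis. This conclusion rests on the text alone.

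The stated 80% was not derived for the QALY result, whose power is unknown. Over the assumed inputs shown, it runs from 11% to 98%. Those figures rest on assumed QALY differences and SDs, a two-sided 0.05 test, and the cost SD and correlation in 2.7. They show that the 80% does not transfer; they do not show a shortfall. The 105 per group also cannot be reproduced from what 2.7 reports, so the 80% for the joint cost and NDI calculation remains unverified.

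**What to change.** - **2.6, 2.8 and Table 2:** name NDI at the three scheduled visits as the effect for the CEA, and QALYs as the effect for the CUA. Replace the parenthesis in 2.8 that defines effectiveness in QALYs with wording that assigns one measure to each analysis.
- **2.7:** state that the 80% refers only to the joint calculation on cost and NDI. Report the willingness to pay per NDI unit and the direction of the EUR 300 difference, so that 105 per group can be reproduced.
- **QALY analysis:** make no power claim. Give the expected precision under stated assumptions instead. At EUR 22,000 per QALY, for example, the half-width of a 95% interval for net benefit is 1.96 × SE, or about EUR 324, 601 and 891 for assumed QALY SDs of 0.05, 0.10 and 0.15.
- **Optional:** report incremental net benefit beside the ICER.

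**Cost.** If NDI is already collected, only wording changes. If it is not, a questionnaire is added at visits already scheduled, and the change must be reported as section 3 requires. That section says outcomes and analyses will not be modified once the first participant is registered, and recruitment was due to start on 1 July 2025. Baseline NDI could not be recovered for anyone already enrolled without it.
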